### Data Collection Instruments

Psychological assessment will be conducted using the DASS-21 questionnaire, as the primary outcome. This questionnaire (21 items) is primarily designed to test emotional states such as depression, anxiety, and stress with three respective subscales each with 7 items. The instrument is known for appropriate psychometric properties and is widely employed. A validated version of the questionnaire in Persian language (27) will be used in the present study with three subscales as the main indicators of the negative emotional and psychological responses. A 4-point Likert scale will be used to test the emotional state of each subscale in the questionnaire. The scale ranges from 0 (does not apply to me at all) to 3 (applied to me very much, or most of the time). As for the total score of each subscale, it ranges from 0 to 21, and a higher score represents a higher level of depression, anxiety, and stress. According to Asghari et al. (27), Cronbach's Alpha test of internal consistency was estimated at 0.94 for the whole scale and 0.85, 0.85, and 0.87, respectively, for depression, anxiety, and stress subscales. Moreover, the intra-class correlation with an absolute agreement between Time 1 and Time 2 assessment occasions for depression, anxiety and stress scales were found to be 0.77 (95% CI: 0.56–0.88), 0.89 (95% CI: 0.81–0.94), and 0.85 (95% CI: 051–0.94), respectively. Intra-class correlation values above 0.74 represent a good reliability (28).

The secondary outcomes (i.e., respiratory/non-respiratory symptoms) will be determined by physician assessment, pulse oximetry, radiology images, kidney and liver function tests, and a thermometer.

In the intervention group, the degree to which the software is used (e.g., seeing the educational content, completing symptoms) and the quantity of questions from care providers will be extracted from the recorded logs of every user and will be reported accordingly.At the end of the research, the survey on the quality of application will be submitted to patients in the intervention group. The information will help to improve the later versions of the application. The questionnaire, derived from the related literature in telemedicine (29, 30), will enquire about users' comments on content domains, presentation design, ease of use, usability and satisfaction. Translation, modification and usage of the questionnaires were based on the opinion of three experts in the field of medical informatics familiar with telemedicine research. After an initial review of the content (of the questionnaires) by the experts, a limited sample of the patients (*n* = 5) also evaluated the instrument to further revise it.

All study content, screening and questionnaire data will be collected through online survey software (Google Form).

### Sample Size

The similar research was used to estimate the sample size. The most similar study to the present work was conducted by Proudfoot et al. (31), who explored the effect of a mobile application on stress, anxiety and depression. In the above-mentioned research, after the intervention, the effect size between the control and intervention group (the one provided with the application) was reported to be 0.41. The sample size is estimated 190 in total (95 for the intervention group and 95 for the control group) which is calculated in G^*^Power software with an effect size of 0.41, error probability of 0.05, power of 0.8, and allocation ratio of 1:1. Regarding the 10 % attrition rate within the study, the goal is to include 105 patients in each group (210 participants overall).

### Randomization

www.randomization.com will be used to create a randomization sequence. The sequence of the generated random number will be inserted into envelopes sealed by an independent researcher (SA), not participating in the main data collection phase or in the intervention. These envelopes will be opened only after the participants sign the informed consent and complete all baseline assessments (FK). Then, the eligible participants will be randomly divided into two groups, a usual care group and an intervention group, which uses the application.

### Blinding

The nature of the intervention is in a way that does not allow for patient blinding. Similarly, the outcome assessor is not blinded either. That is because s/he is constantly in touch with patients in the intervention group to answer the application questions. The data manager (who generates the randomization sequence, prepares envelopes and maintains a list of the participants who already enrolled) and the data analyzer will be completely blinded to the control and intervention group assignment and specifications.

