#### Application Features

The mobile application has been designed with a simple, intuitive user interface.

The application consists of 4 main parts (Figure 2):

**Education:** This part consists of a broad range of educational content during hospitalization and after discharge including psychological, general exercise, medical and health videos and texts about COVID-19 patients. The educational material required for COVID-19 patients will be provided using valid educational resources and experts' consensus.To improve the content in later versions of the software, at the end of each educational medium, the patient will be asked to rate the content and help us increase the quality of services.**Contacting Care Providers:** This part serves the following functions:Support by other medical staff besides the attending physicians such as psychologists who cannot be physically present in the clinic for safety matters.Patient-physician communication via software in hours later than daily visits. Besides filling out an improvement checklist, the patient can write a text about personal queries and concerns.Physician's (or any other therapist's) feedback for patient. Upon seeing the patient's text, the therapist can send a text-based or audio message as the response (to relieve the patient).Contacting care providers will be disabled at the end of the study (2 weeks after discharge).**Symptoms Self-report:** SarveDigital will help COVID-19 patients record their symptoms and, thus, their physician will be able to monitor and control their condition from a distance. Patients will be asked to enter their health symptoms such as fever, sore throat, dry cough, difficulty breathing or the shortness of breath, and loss of taste or smell at least three times a week into the application. Each symptom will be rated on a 4-point scale (e.g., “no fever,” “mild fever,” “moderate fever,” and “high fever”).These data will automatically be sent to the physicians' portal so that the physician will be aware of the patient's health status. It should be noted that the attending physician and the psychologist assigned will be able to access physicians' portal via their mobile phone with a username and password. This will ensure the privacy and security of the patient's information and the relevant classified information (26).**Care Providers' Biography:** This part introduces the key information about the attending physician and psychologist who will communicate with the patient. The aim is to increase the trust the patient places in them to easily share concerns, queries and else.

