#### Secondary Outcomes

Changes to the respiratory symptoms including the respiratory rate will be determined through physician assessment; oxygen saturation will be measured through pulse oximetry; lung involvement will be checked by imaging at the time of discharge.Changes to the non-respiratory symptoms including multi-organ failure will be determined through kidney and liver function tests; fever will be measured with a thermometer; secondary infection will be measured by physician assessment at the time of discharge.

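### The outcome assessor also answers intervention patients' app messages; this dual role is avoidable, and the plan does not keep it away from the DASS-21 or the two physician-assessed outcomes

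*Protocol article*

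**What the plan says.** The Blinding section of the protocol article first says of patients: "The nature of the intervention is in a way that does not allow for patient blinding". It continues: "Similarly, the outcome assessor is not blinded either". The reason given is that "s/he is constantly in touch with patients in the intervention group to answer the application questions". Only the data manager and the data analyst are described as blinded.

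Under Application Features, the replies sent through the app are one of its functions: "Upon seeing the patient's text, the therapist can send a text-based or audio message as the response (to relieve the patient". On who has access at the care providers' end, the same section says that "the attending physician and the psychologist assigned will be able to access physicians' portal". The Control Group section offers nothing comparable. Controls get standard care and, after discharge, a recommendation to use public counselling facilities.

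The primary outcome is the change in DASS-21 from baseline to two weeks after discharge. Patients rate its items from 0 to 3 (Data Collection Instruments). The same section says that "questionnaire data will be collected through online survey software (Google Form"). No section says who, if anyone, is with the patient when the form is filled in.

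Under Secondary Outcomes, respiratory rate is determined by physician assessment, and "secondary infection will be measured by physician assessment at the time of discharge". Oxygen saturation, lung imaging, kidney and liver tests and temperature come from instruments or laboratory tests.

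Strengths and Limitations names the lack of patient blinding and does not mention the assessor's dual role.

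**The concern.** Unblinded patients are inherent in an app trial. An assessor who also delivers part of the treatment is not. The Blinding section links the two as if both followed from the nature of the intervention, yet its only reason for the second is that one person holds two jobs.

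What is at stake is a subjective primary outcome. If the person who has been replying to a patient's worries is present at, prompts or sees that patient's DASS-21, the patient may answer differently, and this can happen in the intervention arm only. Likewise, a clinician who has been corresponding with intervention patients may judge respiratory rate or secondary infection differently in that arm. Neither a blinded analyst nor a larger sample can remove a bias already in the recorded scores.

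**Working it through.** **Step 1: is the dual role stated or inferred?** It is stated. Blinding says that the assessor and the person answering app questions are the same. Application Features makes answering messages a component of the intervention, and Control Group has no equivalent. So the assessor delivers part of the treatment, to one arm.

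**Step 2: which outcomes can it reach?**

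| Outcome | How obtained | Route for bias from the dual role |
|---|---|---|
| DASS-21 (primary) | Patient-rated, online form | Only through presence, prompting or sight of the answers; who administers it is not stated |
| Respiratory rate, secondary infection | Physician assessment | Direct, if the physician also answers app messages; not stated |
| Oxygen saturation, imaging, kidney and liver tests, temperature | Instrument or laboratory | Much less exposed |

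**Step 3: reproduce the plan's sample size.** Inputs from Sample Size and Statistical Analysis: d = 0.41, two-sided alpha 0.05, power 0.80, 1:1 allocation.

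- Normal approximation: n per group = 2(1.960 + 0.842)² / 0.41² = 2 × 7.85 / 0.1681 ≈ 93.4, so 94.
- Two-sample t-test (noncentral t): 94.35, so 95, with power 0.803 at 95 per group.

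The stated 95 per group (190 in total) is reproduced. The abstract gives a different total (112). That is a separate matter, and the Sample Size figure is used here.

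**Step 4: illustrate a bias.** The documents give no bias figure, so the values of b below are assumptions. Let the true effect be zero and let one arm's scores shift by b SD. The t statistic then has noncentrality b × √(n/2), with √(95/2) = 6.892 and 188 degrees of freedom. The rejection rate is the two-sided tail probability at the 5% critical value.

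| Assumed b (SD) | Noncentrality | b / 0.41 | Rejection rate, 95 per group |
|---|---|---|---|
| 0 | 0 | 0% | 5% |
| 0.10 | 0.69 | 24% | 10.5% |
| 0.15 | 1.03 | 37% | 17.7% |
| 0.20 | 1.38 | 49% | about 28% |

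With 105 per group the rates at 0.10 and 0.20 SD are 11.1% and 30.3%, so a larger sample makes the false-positive problem worse.

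**Step 5: what the table does not show.** Patients who know their arm and rate their own mood carry expectation bias whoever handles the form. Any b combines that with the effect of the dual role, and nothing in the documents splits the two.

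**The case against.** The strongest reply is that the DASS-21 is self-rated and all questionnaire data go through an online form. That is compatible with patients completing it alone, in which case the assessor has little to do with the primary outcome. This stands as a limit on the claim. A reader might infer from the term outcome assessor that the app responder collects or scores the DASS-21; no section says so. The route is conditional.

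Other stronger readings also fail:

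- A reader might infer that controls report to a near-stranger. The assessor is not identified. The portal users are the attending physician and a psychologist, and an attending physician may know control patients well.
- A reader might infer that the secondary outcomes as a group are compromised. Only two rest on physician assessment, and it is not stated that the physician rating them answers app messages.
- A reader might infer that the bias must favour the app. That is probable, through a wish to please, but closer rapport could also lead intervention patients to disclose more distress.
- A reader might take 28% as the trial's false-positive rate, or as what separating the roles would save. It is neither.

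It can also be said that the lack of assessor blinding is openly disclosed. That is true, so concealment is not the issue. What remains is that the dual role is presented as a given although staffing can remove it, and that it is absent from the limitations.

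**Conclusion.** The point holds in a limited form. The protocol assigns outcome assessment and the answering of app messages to the same person, and treats this as unavoidable when only patient unblinding is. Differential bias can follow if that person attends, prompts or sees the DASS-21, or rates respiratory rate or secondary infection. The documents neither establish nor exclude these conditions.

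The size is unknown. Under the assumed 0.1 to 0.2 SD, no true effect and 95 per group, the error rate would be about 10.5% to 28%. These figures show that a modest shift matters against a design effect of 0.41; they do not estimate this defect. Confidence is high that the dual role exists and is avoidable, and lower that it reaches the primary outcome. The change is worth making because the outcome is subjective and the remedy uses what the plan already has.

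**What to change.** 1. In Blinding, state that the DASS-21 at discharge and two weeks later is completed by the patient unattended on the existing online form, with an identical link and reminder in both arms.
2. In the same place, state that nobody who answers app messages administers, sees or scores the DASS-21 before database lock.
3. In Secondary Outcomes, label respiratory rate and secondary infection as unblinded assessments.
4. In Strengths and Limitations, add the assessor's dual role beside the lack of patient blinding.
5. If recruitment has started, apply the separation to all remaining assessments in both arms from one date, and report that date and the change.

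Cost: a few sentences and a reallocation of tasks, with no new instrument or procedure. The downsides are slightly more non-response or reading difficulty without a familiar person at hand and, if the change comes during recruitment, possibly two collection modes within the trial. The expectation bias of unblinded patients remains and should be stated as such.

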### Data Management

A management committee (MA, SA, and LAS) is formed to monitor data quality and to approve any decision in the present trial. Data entry and coding will be conducted by people other than the main research team and will be checked by the management committee through range-checks for data values.

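### The data manager is described as completely blinded, yet the same sentence has this role generate the sequence, prepare the envelopes and keep the enrolment list

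*Protocol article*

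**What the plan says.** Three sections of the protocol article bear on this point.

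- **Blinding.** Patients are openly unblinded ("The nature of the intervention is in a way that does not allow for patient blinding"), and so is the outcome assessor. Two roles are said to be masked, the data manager and the data analyzer. The data manager is described as follows: "The data manager (who generates the randomization sequence, prepares envelopes and maintains a list of the participants who already enrolled". Both roles "will be completely blinded to the control and intervention group assignment and specifications".
- **Randomization.** A website produces the sequence; the person who runs it is not named in this section. For the envelopes: "The sequence of the generated random number will be inserted into envelopes sealed by an independent researcher", a person described as "not participating in the main data collection phase or in the intervention". On timing: "These envelopes will be opened only after the participants sign the informed consent and complete all baseline assessments".
- **Data Management.** A three-person committee "is formed to monitor data quality and to approve any decision in the present trial". Data entry and coding are done by people outside the main research team, and the committee checks the result by range checks. The initials given for the independent researcher under Randomization are also among the initials of this committee.

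**The concern.** Complete blinding to assignment and possession of the assignment sequence exclude each other unless something separates the two, and the article describes nothing that does. The contradiction lies inside a single sentence. It therefore does not come from detail that a condensed article leaves to a fuller document.

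It matters because patients and the outcome assessor are unblinded by the article's own account. Masking of the people who handle and analyse the data is the only masking this trial claims. For one of those two roles the claim is incompatible with the tasks assigned to it. A later trial report that repeated the statement would describe a protection that was not in place. A person who knows the allocation while managing data, or while sitting on a body that checks data and approves decisions, is also an avoidable route for bias, even if a modest one.

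**Working it through.** No arithmetic applies, because the point depends on no alpha, power, effect size or sample size. The check sets the assigned tasks against the stated blinding.

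**Step 1: what each task reveals.**

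| Task of the data manager (Blinding section) | What the person then knows |
|---|---|
| Generates the sequence | The arm at each position of the sequence |
| Prepares the envelopes | The arm inside each envelope |
| Keeps the list of enrolled participants | Who has entered and, if the list follows entry, in what order |

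The first two tasks alone give knowledge of the envelope contents. The third supplies the link to people: if envelopes are opened in order, the *k*-th participant on the list received the *k*-th envelope, which holds the *k*-th element of the sequence. In-order use is an assumption; the article does not state it. Without it, the data manager still knows the contents but would also need to know which envelope each participant received.

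**Step 2: could the claim still be true?** There are two ways out:

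- the sequence could use coded arms, with the key held by someone else;
- the enrolment list could be kept in a form that cannot be matched to the envelopes.

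Neither is described in the Randomization, Blinding or Data Management sections.

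**Step 3: does the Randomization section resolve it?** It has the envelopes sealed by an independent researcher, whereas the Blinding section has the data manager prepare them. Two readings are possible.

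- *Same person.* The holder of the sequence is then also a member of the committee that checks data and approves decisions, since the initials coincide. Independence is described only as staying out of main data collection and the intervention. That does not exclude data management or committee work.
- *Different people.* Who fills the envelopes and who only seals them is then unclear. The data manager still generates the sequence and keeps the list, so the blinding claim still fails. The researcher who seals the envelopes still sits on the committee, and the article does not say whether that person sees the contents.

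Under either reading the blinding statement for the data manager is not supported, and the sections need to be reconciled.

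**The case against.** The strongest reply is that this is one badly drafted sentence with little consequence. The outcome is a patient-completed questionnaire, and patients and the assessor are openly unblinded. Those are the dominant routes for bias, and one more person who knows the allocation adds little. Someone always has to know the sequence. The independent researcher and the data manager may be one person, so the two sections need not conflict. Data entry is done by outsiders, and the only committee check described is a range check.

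Much of this stands, and it limits the consequence. It does not rescue the statement. That someone must know the sequence is a reason not to call that person blinded.

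Some larger conclusions might also be inferred, and the article does not support them.

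- *That the data analyzer is unblinded too.* Usage data are collected for one arm only ("In the intervention group, the degree to which the software is used"), and so is the app-quality survey. A file that contained them would reveal the groups. But the analyzer is a separate role with no allocation task, and nothing says that these data are merged into the outcome file.
- *That allocation concealment has failed.* Concealment concerns those who recruit. Envelopes stay sealed until consent and baseline are complete, and an assistant researcher obtains consent. The article does not say that the data manager recruits.
- *That exclusions or the choice of statistical test are biased.* No section gives the data manager either decision. The test choice is tied to a normality check, and an intention-to-treat analysis is stated.
- *That the false-positive rate rises by a known amount.* The article contains no figure from which such a bias could be derived.

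**Conclusion.** The point holds for the data manager. As written, the article claims complete blinding for a role whose listed tasks disclose the allocation. The statement that this person knows the envelope contents follows directly from the tasks. The further statement that this person can link every participant to an arm assumes that envelopes are used in order and that no coded-arm scheme exists; the article is silent on both. The overlap between the independent researcher and the committee is an ambiguity to be reconciled, not proof that one person holds both functions.

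The consequence is moderate and cannot be quantified from the document. No test, sample size or endpoint changes. What is at stake is a false statement about masking and an avoidable route by which knowledge of allocation could reach data handling. It should be corrected, but it does not undermine the trial by itself.

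**What to change.** **Preferred.** Among people already on the team, have the sequence generated and the envelopes prepared and sealed by someone who takes no part in the enrolment list, data management or committee decisions on data until database lock. Let the data manager keep the list without access to the sequence. State in the Randomization, Blinding and Data Management sections, in matching terms, who generates, who fills and seals, who keeps the list and who sits on the committee. In particular, say whether the independent researcher is the data manager.

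**If the roles cannot be separated**, for example because the sequence and envelopes already exist, withdraw the claim that the data manager is blinded and keep it for the data analyzer only.

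**Cost.** The first option means moving tasks between team members; the article does not describe team capacity, so feasibility is for the investigators to judge. The second is a change of wording and gives a less favourable, but accurate, blinding statement.
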